## Methods/design

A pre-post intervention study design is used where HPV vaccination initiation and completion rates are measured before and after the intervention across the same clinics and enrolled participants (Fig. 1). HPV vaccination uptake 18 months before intervention will be queried from electronic medical records (EMR) and Georgia Registry of Immunization Transactions and Services (GRITS), which will serve as the historical control. GRITS is a population-based web application containing consolidated demographic and immunization history information. The use of a concurrent control is to reassess the background HPV uptake rate among PLWH during an adjacent time-period to post-intervention and similar population resources. The comparison of HPV vaccination rates pre- and post-intervention in the three selected representative HIV clinics in Georgia will be an exploratory goal of the trial due to the retrospective approach in the control phase and the prospective approach in the post intervention phase. A “within” analysis will be conducted to compare sites both pre- and post-intervention.

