#### Data analyses of primary outcomes

For analysis of the primary (HPV vaccination initiation) and secondary endpoints (HPV vaccination completion), the uptake rate of HPV vaccination pre- and post-intervention will be estimated separately with a 95% exact confidence interval using all eligible cases from both phases. The one-sample binomial exact test will be used to test whether the rate after the intervention is higher than the baseline rate (P0 = 13.5%). We will also perform the Chi-square test to compare the rate change between control and interventional phases, which will be exploratory. Logistic regression will be used to further adjust background difference in study population in pre- and post- intervention phases. For the longitudinal data collected from the intervention phase, the data structure holds multi-level information from patients, providers, and clinic levels. The goal of the analyses is to identify the factors that might impact HPV uptake from each level of information, which might lead to the future improvement of implementation strategy. Data will be described using summary statistics (e.g., quartiles, median, mean, standard deviation) for continuous variables and marginal distribution (frequency and percentage) for categorical variables. The univariate association with the HPV vaccination (yes vs. no) will be tested in logistic regression for each variable separately. The change of survey response between baseline and a follow-up time point will be tested by paired tests (e.g., paired t-test, McNemar test). Along with data visualization, all above mentioned descriptive and univariate association analyses will be repeated within each of the three clinics. Data will be pooled to build the multilevel analysis models, we mainly consider using the mixed-effect model and/or Bayesian multilevel modeling, in which the random effect will be considered at provider and clinical levels. We will follow the key modeling considerations listed by J.J. Hox [29] to identify the significant mediators and moderators at different levels that impact the uptake of HPV vaccination.

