#### Secondary aims

To assess sustainability, HPV vaccination rates will be calculated at month 36 (12 months post-intervention). The change in HPV vaccination rates between month 24 and month 36 (12 months post-intervention) will be tested by McNemar test. The intervention will be deemed as sustaining its effect if rates of HPV vaccine initiation rates at month 36 remains or increases from month 24’s vaccination rates. To inform future scalability of the program, data from the evaluation and post-evaluation surveys will be described using summary statistics (e.g., quartiles, median, mean, standard deviation) for continuous variables and marginal distribution (frequency and percentage) for categorical variables. The similar analyses will be repeated within each of the three clinics. Additionally, we will conduct a post-intervention focus group consisting of the providers and clinic staff that participated in the program. The qualitative evaluation explore how implementation took place; the barriers to and facilitators of implementation success; ways to address any problems that may have occurred; and recommendations to refine the intervention for scale-up. The focus session will be recorded and transcribed where themes will be extracted and used for adaptation, scale-up considerations, and future research directions.

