#### Statistical power

Based on our preliminary data, we found that HPV vaccination rate is around 13.5% (P0) in general, and another larger study in the literature found a very similar rate of 13.6% [10]. We powered the study to detect an uptake rate > 13.5% after the intervention. Thus, a sample size of 317 achieves 80% power to detect a superiority difference of 5% (PB-P0) using an exact one-sided test with a significance level (alpha) of 0.05. We anticipate a 5% superiority difference is reasonable to achieve with an uptake rate of 18.5% (PB) after the intervention. We will be able to reject the Null hypothesis and claim the uptake rate of > 13.5% after 54 patients have initiated the HPV test. After taking about 15% of the drop-off rate into account, we plan to include 365 participants among 3 clinics for the intervention phase. The calculation was by PASS 2020 for testing superiority of one proportion using the Exact test. The Null hypothesis is *P* < = 13.5% and the alternative hypothesis is *P* > 13.5%. For the control phase, we will query all eligible subjects from EMR database among the 3 clinics at 18 months pre-intervention, which could be approximately 2300 subjects [30]. Assuming we end up with the same number of subjects in both control (*N* = 317) and intervention phase (*N* = 317), we will have 81% statistical power to detect an HPV uptake rate difference of 9% (22.5% vs. 13.5%) by two-sided Fishers’ Exact Test and under significance level of 0.05. We anticipate such a difference would be feasible based on our best knowledge and the literature. Regarding the patient- level component of the intervention, all incoming eligible patients will be influenced, and hence 365 participants are the minimum number to capture the follow-up information, the actual number of sample size used for the calculation of HPV vaccination rate will be larger as the vaccination status will be captured automatically in EMR without a consent.

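### The exploratory pre-post comparison is tested as two independent samples, although the article places the same clinics and participants in both phases and is inconsistent about who forms the control

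*Protocol article*

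**What the plan says.** The protocol article describes the two phases in two ways.

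- **Same people.** Under Methods/design, initiation and completion rates are "measured before and after the intervention across the same clinics and enrolled participants". Under Study outcomes, initiation is measured at baseline (the historical control) and at 24 months post baseline.
- **Two sets of records.** Under Data analyses of primary outcomes, each phase's rate is estimated "using all eligible cases from both phases". Under Statistical power, "we will query all eligible subjects from EMR database among the 3 clinics at 18 months pre-intervention, which could be approximately 2300 subjects". Logistic regression is planned to adjust for differences between the pre and post populations.

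The test is stated as follows: "We will also perform the Chi-square test to compare the rate change between control and interventional phases, which will be exploratory". Its power, 81% for 22.5% against 13.5%, is given for a two-sided Fisher exact test with 317 patients per phase.

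Methods/design also limits the weight of the comparison, which "will be an exploratory goal of the trial due to the retrospective approach in the control phase". The primary analysis is separate: "The one-sample binomial exact test will be used to test whether the rate after the intervention is higher than the baseline rate", with that rate fixed at 13.5%. A paired test (McNemar) is planned under Secondary aims, but only for month 24 against month 36.

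**The concern.** The chi-square test, Fisher's exact test and ordinary logistic regression all require that no patient contributes to both samples. Methods/design says that enrolled participants do. Even without that sentence, the control query takes the eligible patients of the same three clinics that recruit for the intervention phase. Patients in continuing HIV care will very likely appear in both windows. The article gives neither the number who overlap nor a way to handle them.

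This is the only planned test against observed control data from these clinics, and the effectiveness aim is worded as a comparison with the historical baseline. Its p-value and interval should match the way the data arise.

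**Working it through.** **1. The plan's own power figure.** Inputs (Statistical power): 317 per phase, 13.5% and 22.5%, two-sided Fisher exact test, alpha 0.05. Full enumeration of two independent binomials gives 81.8%, against 81% stated. The figure reproduces, and it is an independent-samples figure.

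**2. Variance with overlap.** Let n0 and n1 be the phase sizes, m the number of patients in both, v = p(1 − p), and r the within-patient correlation. Then

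Var(difference) = v0/n0 + v1/n1 − 2·m·r·√(v0·v1)/(n0·n1).

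The independent-samples tests omit the last term. The article gives neither m nor r, so both are assumed over a range. The largest possible r is p0(1 − p1)/√(v0·v1), reached when status can never reverse:
- 13.5% and 22.5%: 0.135 × 0.775/√(0.116775 × 0.174375) = 0.73
- 13.5% and 18.5%: 0.135 × 0.815/√(0.116775 × 0.150775) = 0.83

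**3. Full pairing, 317 and 317, 13.5% vs 22.5%.** The independent SE is √((0.116775 + 0.174375)/317) = 0.0303.

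| r | Correct SE | Correct / independent |
|---|---|---|
| 0.1 | 0.0288 | 0.95 |
| 0.3 | 0.0255 | 0.84 |
| 0.5 | 0.0216 | 0.71 |
| 0.73 | 0.0161 | 0.53 |

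At the extreme, the independent SE is too large by 0.0303/0.0161 = 1.9. With half of the patients overlapping, the ratio runs from 0.98 to 0.80.

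**4. Full pairing, 13.5% vs 18.5%, status cannot reverse.** Independent SE √((0.116775 + 0.150775)/317) = 0.0291. Paired SE √((0.05 − 0.0025)/317) = 0.0122. The factor is 2.4.

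**5. The planned control size, 2300 vs 317, all 317 among the 2300, r at its maximum.**
- 22.5%: independent √(0.116775/2300 + 0.174375/317) = 0.0245; correct 0.0226; ratio 0.92
- 18.5%: independent √(0.116775/2300 + 0.150775/317) = 0.0229; correct 0.0208; ratio 0.90

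The correct SE is thus 8 to 10% smaller at most.

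**6. Where the study may fall.** Statistical power adds that the post-intervention rate will rest on more than the 365 enrolled, because EMR status is captured without consent. If the post set approached the control set (assumed 2300 and 2300, full overlap), the ratios in step 3 would apply again.

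**7. The opposing force.** Let uptake vary by clinic and period with an assumed intraclass correlation of 0.001, 0.005 or 0.01, and 317/3 ≈ 106 patients per clinic and phase. Then √(1 + (317/3 − 1) × ICC) raises the SE by 1.05, 1.23 or 1.43.

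**The case against.** The strongest case is that a paired sample is not established. The operational sections describe a retrospective EMR cohort against a prospective phase and adjust for population differences, which would make little sense for identical people. This stands. A reader might infer from Methods/design that every patient is measured twice and that the chi-square test discards most of the information. With 43 rising to 59 initiators among 317, Pearson's test gives p = 0.084 and exact McNemar (16 vs 0) gives p = 0.00003. The arithmetic is right, but it describes only the full-overlap, cumulative-status extreme.

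Nor would that small paired p-value show an effect. Ever-initiated status can only rise: 6 new initiators among 317 (1.9%) already give p = 2 × 0.5⁶ = 0.031 with no intervention needed. Plain McNemar is therefore no remedy, and clustering on patient while keeping cumulative status has the same fault.

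It can also be said that if uptake means a first dose within each window among patients still unvaccinated, a patient can have the event only once, and ordinary logistic regression needs little or no correction for overlap. That is correct, but the article does not fix this definition. Its month 24 against month 36 test is also not an exact parallel, since both of those time points follow the intervention.

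Finally, the comparison is labelled exploratory, and record handling is often left to an analysis plan. That lowers the weight of the point. It does not remove the contradiction over who is compared, which lies in the article itself.

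**Conclusion.** The point holds in a limited form. The article contradicts itself on whether the control is the same patients or an EMR cohort, and its tests assume an independence that overlapping patients would break.

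On patient overlap alone the test is conservative. The correct SE is at most 8 to 10% smaller with 2300 vs 317, and the overstatement reaches 1.9-fold or 2.4-fold only under full pairing with status that cannot reverse. These bounds rest on assumed overlap and correlation. Clinic-by-period variation works in the opposite direction, so the documents do not support a claim that the final p-value is too large, or too small.

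A reader might also infer that the trial's main conclusion is at risk. It is not, on this point: the primary exact test compares the post-intervention rate with a fixed 13.5% and uses no pre-phase records. This should be corrected, but it does not undermine the primary analysis.

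**What to change.** 1. Reconcile Methods/design, Data analyses of primary outcomes and Statistical power on who forms the control: the enrolled patients, a separate EMR cohort, or a mixture.
2. Define the outcome in both phases as new initiation within windows of equal length, among patients not yet initiated at the start of the window. At present the look-back is 18 months and the outcome is read at 24 months.
3. Link patients across phases by EMR/GRITS identifier, and report how many are in both.
4. Replace the chi-square test and ordinary logistic regression with a logistic model that has patient-clustered (GEE or robust) standard errors and clinic as a fixed effect. The fixed effect removes stable clinic differences. It does not remove clinic-by-period variation, which three clinics cannot estimate well, so the result should be reported with that caveat.
5. Label the 81% power as an independent-samples figure.

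The cost is wording in the analysis plan and slightly more linkage and analysis work. Restricting to patients not yet initiated changes the denominator, so the report should say whether the resulting rate is comparable with the fixed 13.5%.

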### Data analysis plan

#### Study outcomes

Initiation of the HPV vaccine is the primary outcome endpoint (Fig. 2). Initiation of the HPV vaccine is defined as receiving the first or second immunization from the series. This variable will be measured by electronic medical records and GRITS at baseline (historical control) and 24 months post baseline. We hypothesize the initiation rate will be higher than the historical control rate. Completion of the HPV vaccine is the secondary outcome variable. Completion is defined as receiving all three immunizations from the series, regardless of time. This variable will be measured by electronic medical records and GRITS baseline (control) and 24 months post baseline.

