#### Process evaluation

The RE-AIM (Reach, Effectiveness/Efficacy, Adoption, Implementation, Maintenance) framework will guide planning, implementation, and evaluation of the 4 Pillars™ program. The study’s reach will be estimated from a quantitative perspective by estimating the target population that was exposed to the intervention. The clinic’s patient census data during the period of the implementation phase will be used to estimate the likely reach of the program across sites. Intervention effectiveness and efficacy will be measured by the change in uptake rate of vaccination (i.e., intervention effectiveness). We will calculate the percent change in initiation of the vaccine and percent change in completion of the vaccine from the control phase and 24 months post intervention, after adjusting for demographics differences (age, gender, race, healthcare insurance) in population. Providers and clinic staff will be asked to complete an evaluation of HPV vaccination progress every 3-months. We will also collect qualitative data from feedback sessions with the immunization champions to assess opportunities for and barriers to adoption. The post-evaluation interviews with providers and staff who implemented the program will assess extent of involvement, acceptance of the intervention, implementation fidelity, and extent of organizational spread of the intervention. We will assess the frequency, duration, and the extent to which the intervention was implemented as planned, participation attendance, and costs of implementation, as measured via the intervention and post-intervention evaluations. Intervention sustainability will be measured as the gains or maintenance of HPV vaccination rates post-delivery of the intervention. HPV vaccination rates will be calculated via EMR and GRITS at month 36 (12 months post intervention) and compare to HPV vaccination rates at month 24. Follow up assessments will measure penetration or the extent to which recommendation and administration of the HPV vaccination is integrated within the clinic.

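### The control rate covers 18 months and the post-intervention rate 24, with no adjustment for window length; the primary benchmark of 13.5% has no stated window at all

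*Protocol article*

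**What the plan says.** All references are to the protocol article.

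- **Control window.** Methods/design: "HPV vaccination uptake 18 months before intervention will be queried from electronic medical records (EMR" and the state immunisation registry. Statistical power repeats the figure and gives the expected number: "we will query all eligible subjects from EMR database among the 3 clinics at 18 months pre-intervention, which could be approximately 2300 subjects".
- **Post window.** Study outcomes says of initiation: "This variable will be measured by electronic medical records and GRITS at baseline (historical control) and 24 months post baseline". Completion has the same timing.
- **Effectiveness measure under RE-AIM.** Process evaluation takes the percent change "from the control phase and 24 months post intervention, after adjusting for demographics differences (age, gender, race, healthcare insurance) in population". The same section dates the sustainability assessment "at month 36 (12 months post intervention".
- **Tests.** Under Data analyses of primary outcomes, the primary test is a one-sample exact binomial test against a fixed P0 of 13.5%. The chi-square comparison of the two phases is labelled exploratory. A logistic regression adjusts for differences in population background.
- **Source of P0.** Statistical power attributes 13.5% to preliminary data and cites a similar literature figure. It gives no observation period for either.

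**The concern.** Both phases are summarised as the proportion of patients who have started the vaccine. With any steady background uptake, that proportion is larger after 24 months than after 18. The adjustments described cover patient characteristics and not length of observation, so the extra six months would be credited to the programme. This is more than detail left to an analysis plan, because the article itself fixes the two windows and fixes them unequally.

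The direct effect is on the chi-square comparison, the logistic model of the two phases and the RE-AIM percent change. The primary test has a related but separate problem: a 24-month outcome is judged against a benchmark whose period is unknown. The study is powered for a 5-point gain, so a 4-point artefact would matter there too.

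**Working it through.** **Inputs.** Control window 18 months (Methods/design; Statistical power). Post window 24 months (Study outcomes). P0 = 13.5%, planned rate 18.5%, one-sided alpha 0.05, N = 317, cut-off 54, enrolment 365, about 2300 control records (all Statistical power).

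**The plan's own rule.** Exact binomial at 13.5%: P(X ≥ 54 | 317) = 0.042 and P(X ≥ 53 | 317) = 0.058, so the cut-off of 54 reproduces. N = 317 reproduces by the normal approximation (316.1, rounded up). Exact power at 18.5% with this cut-off is 77%, slightly under the stated 80%. If all 365 are analysed the cut-off is 61, with exact alpha 0.046.

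**Effect of six extra months with no programme effect.** Assume 13.5% initiate in 18 months at a constant hazard:

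p24 = 1 − (1 − 0.135)^(24/18) = 0.176

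The artefact is 17.6 − 13.5 = 4.1 points, against the 5 points the study is powered to find. As a percent change it is 4.1/13.5 ≈ 30%. Linear accrual gives 13.5 × 24/18 = 18.0%.

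**Phase comparison** (18 versus 24 months applies directly; two-sided 0.05; true rates 13.5% and 17.6%; everyone followed for 24 months):

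| Control vs post | Fisher exact | Normal approximation |
|---|---|---|
| 317 vs 317 | 26% | 29% |
| 2300 vs 317 | 47% | 50% |
| 2300 vs 365 | 52% | 55% |

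Statistical power also foresees a post-phase denominator larger than 365, taken from the medical records. At 2300 versus 2300 the figure would be about 97% (normal approximation).

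**Primary test** (false-success probability with no programme effect). The answer depends on the unstated window of P0:

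| If P0 = 13.5% is a rate over | 24-month rate | P(X ≥ 54 of 317) |
|---|---|---|
| 18 months | 17.6% | 62% |
| 21 months | 15.3% | 21% |
| 24 months | 13.5% | 4% |

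With P0 as an 18-month rate, the figure is 69% at N = 365 (cut-off 61). Linear accrual gives 69% at N = 317 and 76% at N = 365.

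**Sensitivity, P0 taken as an 18-month rate, N = 317.** If actual follow-up averages 22 months the probability is 37%; at 21 months, 26%; at 18 months, 4%. If only 30% of patients would ever accept the vaccine, it is 42% at 24 months.

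**Timing wording.** Process evaluation places effectiveness "from the control phase and 24 months post intervention". It also equates month 36 with 12 months after the intervention, which makes month 24 the end of the intervention (36 − 12 = 24). Both cannot hold.

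**The case against.** The strongest objection is that success is judged against a fixed P0, not against the 18-month query. P0 comes from preliminary data, is described as a general rate, and rests on a literature figure reported simply as initiation. It could be ever-vaccinated prevalence, in which case the 24/18 scaling has no bearing on the primary test. A reader might infer from the unequal windows that an ineffective programme would probably be declared a success, but the documents do not support that unconditionally. The opposite is not established either: the article calls P0 the baseline rate, equates baseline with the historical control, and uses 13.5% as the control-phase rate in its second power calculation. The 18-month reading is therefore supported but not stated.

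Second, the comparison where 18 versus 24 months applies directly is declared exploratory. This limits the consequence. However, the reason given is retrospective versus prospective data collection, so readers are not warned about unequal windows, and the RE-AIM percent change makes the same comparison.

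Third, the figures assume a closed cohort, a constant hazard and 24 months for every patient. Enrolment spread over the intervention period would shorten follow-up and reduce the bias, and an open denominator would alter it. This stands, and the sensitivity figures show how much it matters.

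Fourth, the 18 months could be read as a time point instead of a look-back. The period covered by the control rate would then be undefined, which also needs correcting.

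**Conclusion.** The window mismatch holds. As written, the phase comparison and the RE-AIM percent change set an 18-month proportion against a 24-month one with no correction. Under constant uptake, a constant hazard and full follow-up, this produces a spurious gain of about 4 points. The exploratory test would then be falsely significant about 26–29% of the time at the planned 317 versus 317, and roughly 47–55% against 2300 controls.

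For the primary test the conclusion is conditional. False success is about 62–69% if P0 is an 18-month rate and every patient is followed for 24 months. It falls to 26% if follow-up averages 21 months, and is about 4% if P0 is a 24-month rate. If P0 is ever-vaccinated prevalence, the scaling does not apply. What holds in every case is that the primary benchmark has no stated period while the outcome it judges has one. The contradictory dating of month 24 is a separate wording error that depends on none of these assumptions.

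**What to change.** 1. **Equal windows in the phase comparison and the RE-AIM measure.** Extend the look-back to 24 months or truncate the post period at 18 months, for both initiation and completion. Alternatively, compare initiation per person-month at risk using recorded dose dates. This changes the query dates or the analysis wording; it needs no new patients or data source.
2. **State the window of P0 and evaluate the primary outcome over the same window.** Extending the look-back alone does not touch the primary test, because P0 is fixed. If P0 is an 18-month rate, truncating the primary outcome at 18 months keeps the 54-of-317 rule. Re-basing P0 to 24 months is not free: at 17.6% the cut-off at N = 317 becomes 68 (exact alpha 0.044) and power at the planned 18.5% is about 10%, so the target rate, cut-off and power would have to be restated. If P0 is ever-vaccinated prevalence, say so and define the outcome to match.
3. **Reconcile the timing in Process evaluation** so that the effectiveness time point agrees with month 36 being 12 months after the intervention. This is one line of text.
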